## Abstract

Chronic health conditions in children and young people can have a significant impact on their ability to maintain engagement in school, education, and learning. While this functional limitation affects only about 1.6% of all children and young people, the absolute number is not inconsequential. In Australia, for example, the number is in the order of 67,000 children and young people. Furthermore, research has shown that this group of young learners are at increased risk of lower academic, social, and emotional and quality of life outcomes than their healthy peers, both in the short and the longer term. For this reason, most pediatric hospitals in western developed countries have hospital-based schools that aim to prevent children and young people with a chronic health condition from disengaging from school, education, and learning. However, there is a lack of robust evidence of the effectiveness of these education support programs. This protocol for a feasibility study of the effectiveness of evaluating an education support program in Australia aims to identify a priori the methodological key features of a robust trial, including developing an answerable research question, choosing a controlled study design that compares the outcomes of both an intervention group and a well-matched non-intervention or control group, eligibility criteria, important and validated outcome measures such as quality of life, and how statistical data should be analyzed and reported. Lessons learned from the proposed feasibility study will be used to inform a larger-scale study.

Pediatric chronic health conditions are defined as illnesses that have lasted, or are expected to last, at least six months; have a pattern of recurrence or deterioration; have a poor prognosis; and produce consequences or sequelae that impact on the individual’s quality of life (Australian Institute of Health and Welfare [AIHW], 2005; Martinez & Ercikan, 2009). Common childhood chronic health conditions include cancer, cystic fibrosis, Crohn’s disease, diabetes, epilepsy, and asthma. Approximately 20%–30% of children and young people are reported to have a chronic health condition, depending on the definition used. A relatively small percentage (1.6%) have a chronic health condition that is severe enough to impact on their functional ability to regularly attend school (Shaw & McCabe, 2008). In Australia this amounts to around 67,000 students.

For this reason, most pediatric hospitals in western developed countries have hospital-based schools or education support services. For example, the Children’s Hospital School at Great Ormond Street Hospital, London, aims to minimize the interruption and disruption to children and young people’s education so that academic progress and an interest in learning will continue, as far as medical circumstances permit. Similarly, at the Hasbro Children’s Hospital, Rhode Island, in the United States, the hospital school has the following aims: to make the transition from hospital back to school as smooth as possible for the patient and classmates, to maintain academic involvement with the patient’s home school and teachers, and to utilize hospitalization as a unique and positive learning experience. And in Melbourne, Australia, teachers at the Education Institute at the Royal Children’s Hospital work with more than 2,000 school-aged students each year to keep them engaged with their education and connected to their regular school and classmates.

The rationale for these education support programs is that children and young people with chronic health conditions are at increased risk of disengagement from school, education, and learning, and, worse, academic, social, and emotional and quality of life outcomes both in the short and the longer term (Martinez & Ercikan, 2009; Maslow, Haydon, McRee, & Halpern, 2012; Nasuuna, Santoro, Kremer, & Silva, 2016). Furthermore, access to a quality education for all children, including those managing a chronic health condition, is a right that is enshrined in both national and international laws (UNICEF, 2006).

While the common goal of education support programs is to prevent students with a chronic health condition from disengaging from school, education, and learning and to maintain continuity in their human development processes (Seymour, 2004), many different types of services or interventions exist for this group of students, shaped by their setting and context, and described differently (Dempsey, 2019). Nonetheless, there appear to be some common elements or themes to these programs (Capurso & Dennis, 2017). The description of the education support program at the Queensland Children’s Hospital, Australia, funded by the State Department of Education, reflects many of the key common themes of education support programs, as described by Capurso and Dennis (2017). They are:

Students have access to learning at all stages of their illness.Staff deliver high-quality teaching and learning programs.Students experience continuity of learning.Students and staff feel a sense of belonging to their school communities.Staff engage in multidisciplinary collaboration.

According to Bond (2019), each of these main themes may be further broken down into a series of variables that render the five key elements effective, as shown in Figure 1.

**Figure 1 F1:**
[figure not shown]
Best practice in education support for hospitalized students in Queensland, Australia.

However, there is a need to generate more robust evidence about the effectiveness of these types of education support programs. A systematic review of educational support services for children and adolescents with chronic health conditions (Barnett, 2018) found just four controlled studies of a diverse range of education support programs aimed mostly at children with cancer, and inconclusive evidence about their effectiveness. It also revealed that the current state of the evidence about the effectiveness of these interventions is predominantly made up of qualitative research, case studies, and expert opinion, which are known to be more affected by bias than more rigorous controlled studies that include both an intervention group and a comparison or control group (Chalmers, 2005).

## The Present Study

To fill this gap, the purpose of this paper, therefore, was to consider how a more rigorous controlled study of the effectiveness of education support services for students with chronic health conditions could be undertaken. Specifically, it outlines the protocol for a feasibility study as a first stage to evaluating the effectiveness of these programs. Feasibility studies are considered useful as preparation for the conduct of a larger controlled evaluation of complex interventions (Thabane et al., 2016), with the goal of reducing uncertainty and thereby increasing the chance of a successful larger study (Thabane et al., 2016). The proposed protocol is based upon and includes recommended and relevant sections of the Standard Protocol Items: Recommendations for Interventional Trials (SPIRIT) checklist (Chan, Altman, Dickersin, & Moher, 2013).

Specifically, the aims of the feasibility study are to:

Examine the effectiveness of an education support program for school-aged students with chronic health conditions on their engagement in education and learning, and quality of life;Trial the recruitment and retention of study participants;Identify and trial the use of validated outcome measures;Obtain feedback from stakeholders about the feasibility of the above with the view of conducting a larger scale trial.

## Method

### Study Design and Setting

Many researchers (e.g., Chalmers, 2005; Gray, 2001; Littell & Shlonsky, 2010; Shlonsky & Gibbs, 2004) consider the randomized controlled trial (RCT) the “gold standard” in effectiveness evaluations as it is viewed to be the best design for minimizing the influence of bias. But for many others in the pedagogical community, the debate on this point is still open (Biesta, 2007). In our circumstance, given that access to a quality education is a right of the child along with the potential public sensitivity of randomly allocating hospitalized children and young people to either receive education support or not while in hospital, an RCT may not be considered either appropriate or ethical.

Fortunately, other controlled study designs are available for consideration. Controlled studies (i.e., studies with both an intervention group and a well-matched non-intervention or control group) are considered best for evaluating the effectiveness of an intervention because they state the counterfactual. That is, they investigate and compare both what happens if a group of people receive the intervention and what happens if a group of people don’t receive the intervention. This, in turn, allows stronger and more robust claims of causality and effectiveness of a given intervention; that is, that any differences in results between the two groups were due and can be attributed to the intervention (Chalmers, 2005; Shlonsky & Gibbs, 2004).

One such design is that of a controlled cohort study, where both the intervention group and the control group exist “naturally” in the community. Such is the case in Victoria, Australia, where the Department of Education and Training (DET) funds education support programs at some, but not all, pediatric hospitals and departments. The DET funds education programs at two pediatric hospitals (Royal Children’s Hospital and Monash Children’s Hospital), but not four regional pediatric departments in hospitals in Warrnambool, Ballarat, Gippsland, and La Trobe. Children and young people with chronic illnesses admitted to the latter hospitals where there is no funded education support program, therefore, naturally form the control or comparison group.

The subjects for the current study consisted of the children and young people under treatment for a chronic health condition at the Royal Children’s Hospital (the intervention group) and the four regional hospitals.

### Developing an Answerable Research Question

An important first step in effectiveness evaluations is to develop an answerable research question in PICO format (Shlonsky & Gibbs, 2004). The general and overarching aims of education support programs have been discussed earlier. As such, the specific research question for our evaluation of the effectiveness of education support programs in Victoria, Australia, is as follows.

**Table d66e222:** 

Population (P)	Do hospitalized children with a chronic health condition,
Intervention (I)	who receive hospital-based education support
Comparison (C)	as compared to those who receive no hospital-based education support,
Outcomes (O)	have higher levels of engagement in education and learning and quality of life?

### Participants

Participants will need to meet the following eligibility criteria:

Being school aged (5–17 years old)Having a chronic illness (for example, but not limited to, cancer, cystic fibrosis, eating disorder and Crohn’s disease/renal failure)Having an expected length of stay (LOS) in hospital of five or more days in a six-month period

The criterion of an expected LOS of 5+ days was informed by the work of [name] and colleagues, whose Australian research investigated the impact of school absence on academic performance. Their study (Hancock, Shepherd, Lawrence, & Zubrick, 2013) was based on students who were enrolled in the public school system in Western Australia from 2008 to 2012. The data included information collected by schools on students and their caregivers upon enrolment, attendance records, and the results of the National Assessment Program – Literacy and Numeracy (NAPLAN). The authors hypothesised a threshold effect of absence from school on academic performance, such that a small amount of absence from school might have minimal effect on academic performance, but beyond some threshold attendance level there would be a noticeable drop in measured academic performance. Their findings, however, generally support the notion that “every day counts.” That is, every day of absence from school is associated with progressively lower achievement in numeracy, writing, and reading.

They also found that, generally, an absence of four weeks per half year resulted in performance dropping to that of the national minimum standard. However, school absence had a much greater influence on the achievement of students in lower socio-economic index schools with absences of three weeks per half year resulting in performance dropping to that of the national minimum standard.

In earlier research on categories of at-risk attendance, again in the Western Australian school jurisdiction and based on empirical findings from the 1993 Western Australian Child Health Survey (WACHS), Zubrick, Silburn, Gurrin, and Shepherd (1997) found that students who were, on average, absent for two weeks per half year would be considered to be at-risk for lower academic competence.

Furthermore, in 2014 the Royal Children’s Hospital Education Institute undertook an investigation into what happens when the young people/students they had worked with were discharged from hospital. Results showed that one month after discharge, one in three children were still at home and had not returned to school. Of the children who had returned to school during the month after discharge, two out of three spent a period of time at home prior to returning to school – the average length of time spent at home prior to returning to school was 13 days (ARACY, 2015).

For these reasons, in this feasibility study, the eligibility criterion of an expected in-hospital LOS of 5 or more days in a six-month period was chosen as a proxy measure of an expected total length of absence from school of potentially 14 (or more) days in a six-month period. Such a length of absence would put the child in an “at-risk” category of worse academic outcomes.

### Intervention to Be Tested

The education support program at the Royal Children’s Hospital (RCH) in Australia is funded by the Victorian DET and employ qualified teachers to work with hospitalized young people/students to help maintain engagement with the students’ regular schools and peers, and engagement in education and learning. The Education Institute teachers evaluate new patients to determine the appropriate level of educational support. Evaluations are based on need or educational risk, with eligible students being offered individual or group learning sessions, or a combination of both. Each student receives an Individual Learning Plan (ILP) prepared in collaboration with the student, families/carers, and the enrolled educational setting. The ILP is reviewed regularly and updated in line with the student’s educational progress. The hospital kindergarten program is led by qualified early childhood educators who, through engaging play-based learning, help prepare children for school. To be eligible for the program, children must be at least 4 years old before April 30 in the year of enrolment. The Education Institute offers an evidence-based program built on high-impact teaching strategies, with a focus on literacy and numeracy underpinned by the Victorian Curriculum.

Elements of the education support program are described in a program logic model developed in consultation with staff from the Centre for Program Evaluation at the University of Melbourne. It depicts a socio-ecological approach that recognizes the influence of a number of spheres within which the child functions on a daily basis (Bronfenbrenner, 1995). These include the spheres or levels of the individual, family, schools, community and service systems. (For more detail, see Figure 2: Logic Model of an Education Support Program for Children and Young People with a Chronic Health Condition; Barnett, 2018.) The key activities and variables of the intervention across the first three spheres are listed in Table 1. Finally, the education support model at the RCH also reflects the five common themes of pediatric hospital-based education support programs as described in the introduction.

**Figure 2 F2:**
[figure not shown]
Logic Model of an Education Support Program for Children and Young People with a Chronic Health Condition.

**Table 1 T1:** Key activities of education support programs for hospitalized students with chronic health conditions.

Sphere of influence/level	Key activities of education support

Individual young person	Assist children stay connected to their school, teachers and peers Develop/Implement an Individual Learning Plan (ILP) Deliver group and one-to-one learning opportunities Use inquiry/problem solving strategies to explore student’s passions about real world topics
Family	Meet and consult with families about their child’s learning needs Support parents as advocates of their child’s right to education Meet and consult with families about their coping Provide parents with information, resources & referrals
School	Liaise with teachers so the child’s learning needs continue to be identified and met throughout their healthcare journey: hospital, home and return to school Together with the healthcare team, assist schools prepare for the child’s transition back to school: workshops with teachers and peers

### Ethics

Ethics approval will be obtained for the study from a registered Australian Human Research Ethics Committee prior to commencement of the research.

### Recruitment and Consent

Approval to undertake the feasibility study will be sought from the Victorian DET. Once such approval has been obtained, all five pediatric sites (one pediatric hospital as the intervention site and four regional hospitals with pediatric wards as the control sites) will be approached by the lead researcher and invited to participate in the feasibility study. Once consent has been obtained from these two levels, we will proceed with the rolling recruitment of individual young people. Specifically, all new inpatients as they present to hospital and who meet the eligibility criteria will be approached by the lead researcher and asked if they would participate in the trial. Both the young person and his or her parent/s or caregiver/s will receive a Plain Language Statement about the study and asked to provide written consent.

For aim number 4 (Obtain feedback from stakeholders about the feasibility of the above with the view of conducting a larger scale trial), we will identify two key stakeholders at each of the five locations and ask them to participate in semi-structured interviews with the lead researcher. The purpose of the interviews will be explained, and verbal consent will be obtained and recorded by the lead researcher.

### Sample Size and Power Analysis

Sample size calculations were run to determine the number of participants required in the study to have an 80% chance of detecting a 0.3 standard deviation effect of the intervention based on the results of the outcome measures. Based on these criteria, we would need complete data from 180 participants in each arm of the study. Attrition and loss to follow-up is considered to be low, in the order of 25%.

As such, we would need to recruit 240 participants to each arm of the study. However, as this is a feasibility study, we will recruit 40 participants to each arm of the trial and evaluate the procedure used, time, and feasibility of achieving a larger sample for any future larger-scale study.

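### The 180-per-arm figure for 80% power assumes independent children, but exposure is set by hospital, one against four, and a single intervention hospital cannot be told apart from its programme

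*Protocol article*

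**What the plan says.** The Sample Size and Power Analysis section sets out to "have an 80% chance of detecting a 0.3 standard deviation effect of the intervention" and concludes: "Based on these criteria, we would need complete data from 180 participants in each arm of the study". After 25% attrition, "we would need to recruit 240 participants to each arm of the study". It then says that, because this is a feasibility study, 40 per arm will be recruited and used to judge whether a larger sample is achievable. It states no significance level, intra-hospital correlation, design effect or number of hospitals.

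The arms are defined by hospital. Under Study Design and Setting, children admitted where no programme is funded form the comparison group. Recruitment and Consent fixes the layout as "one pediatric hospital as the intervention site and four regional hospitals with pediatric wards as the control sites". Data Analysis plans ANOVA by group with control for the listed confounders. Those in the Confounders section are all family or parent characteristics: socio-economic position, parental involvement in schooling, and parental mental health.

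Aim 1 is to examine the programme's effectiveness. In its general case for controlled studies, Study Design and Setting says that such designs support the claim that "any differences in results between the two groups were due and can be attributed to the intervention".

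**The concern.** A sample size for independent children is set beside a design in which every child's exposure is decided by the hospital. Children at one hospital share case mix, referral pattern, staff and catchment. Any outcome variation between hospitals adds to the variance of the group difference, and it shrinks with the number of hospitals, not with the number of children. One arm has a single hospital, so this component stays large and cannot be estimated within that arm.

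Two things are at stake. First, 240 per arm is the benchmark against which the feasibility of a larger study will be judged, and it could be carried forward as sufficient when it is not. Second, the aim 1 result could be read as a programme effect when it is equally a difference between one dedicated pediatric hospital and four regional departments.

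**Working it through.** **Inputs.** From the Sample Size section: effect 0.3 SD, power 80%, 180 complete per arm, 25% attrition, 40 recruited per arm. From Recruitment and Consent: 1 versus 4 hospitals. Assumed here: two-sided 5% (one-sided 5% gives 138 per arm and does not fit); four control hospitals of equal size; ICC from 0 to 0.05, since none is given; between-hospital variance treated as known.

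**Step 1: reproduce the plan's figure.** For independent children, n per arm = 2 × (1.960 + 0.842)² / 0.3² = 174.4, so 175. The t-test version gives 175.4, so 176. At 180 per arm, power is 81%. Attrition: 180 / 0.75 = 240 exactly. The small gap from 176 to 180 is consistent with rounding and leaves no visible allowance for hospital.

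**Step 2: power at 180 per arm with 1 versus 4 hospitals.** With total SD 1:

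Var(difference) = ICC × (1 + 1/4) + (1 − ICC) × 2/180

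Power = Φ(0.3 / SE − 1.96)

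Example at ICC 0.01: 0.0125 + 0.0110 = 0.0235; SE = 0.153; 0.3/0.153 − 1.96 ≈ 0; power about 50%.

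| Assumed ICC | Variance | Power at 180 per arm | Children per arm for 80% |
|---|---|---|---|
| 0 | 0.0111 | 81% | 175 |
| 0.001 | 0.0124 | 77% | 196 |
| 0.005 | 0.0173 | 63% | 382 |
| 0.01 | 0.0235 | 50% | not reachable |
| 0.02 | 0.0359 | 35% | not reachable |
| 0.05 | 0.0731 | 20% | not reachable |

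**Step 3: where 80% is lost.** Power of 80% needs a variance of at most (0.3 / 2.802)² = 0.01147. At 180 per arm this is exceeded once the ICC passes about 0.0003. With unlimited children the variance cannot fall below 1.25 × ICC, so 80% is out of reach at these five sites above ICC = 0.01147 / 1.25 = 0.0092.

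These values are optimistic. If between-hospital variance must be estimated, with 5 − 2 = 3 degrees of freedom, power at ICC 0.01 is about 28%.

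**Step 4: the study actually run.** 40 × 0.75 = 30 completers per arm. The type I error of a comparison that ignores hospital is 2 × [1 − Φ(1.96 × √((2/30) / V))], with V = 1.25 × ICC + (1 − ICC) × 2/30.

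| Assumed ICC | V | Type I error at 30 per arm |
|---|---|---|
| 0.01 | 0.0785 | 7% |
| 0.02 | 0.0903 | 9% |
| 0.05 | 0.1258 | 15% |

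**Step 5: programme versus hospital.** This needs no ICC. Every intervention child is at one hospital and no control child is, so the group indicator and the indicator for that hospital are the same column. No covariate measured on families, and no added children, can separate them.

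**The case against.** The strongest reply is that the section does not power the study being run. It moves straight on to 40 per arm, claims no power there, and leaves the sites of a future study open. This stands. A reader might infer that the protocol promises 80% power and fails to deliver it, but the documents do not support that. The figures in Step 2 are conditional on the larger study keeping one versus four hospitals. Against this, the section speaks of "Sample size calculations were run to determine the number of participants required in the study", and no other layout is described anywhere.

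Second, every ICC here is assumed. The relevant one is what remains after adjustment for family factors, and the primary outcome concerns the child's own school, so hospital need not be a strong cluster. At 0.001 the loss is small: 77% power, or 196 per arm. This stands as to size, which is why a range is shown.

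Third, the attribution sentence closes a general paragraph on controlled studies. A reader might take it as this study's own results claim, but it is not worded as one. The next paragraph does present the present design as one of that kind, so a caveat specific to it is fair.

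Fourth, a reader might call the lack of a named hospital term in the ANOVA an error. It is not: a journal article can leave model detail to an analysis plan, and a fixed hospital term would be aliased with arm anyway.

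Fifth, a reader might count leaving out the second funded hospital as a defect. It is a trade-off. The target is the Royal Children's Hospital programme, the other hospital's programme is not described, and pooling could mix two interventions. At 180 per arm, 2 versus 4 sites would still give only 60%, 46% and 28% power at ICC 0.01, 0.02 and 0.05.

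**Conclusion.** The point holds as a fault of assumption, not of arithmetic. The 180 and 240 are correctly computed for independent children, but the design described is not of that kind. If a larger study keeps one versus four hospitals, 80% power survives only at an ICC of essentially zero. The loss runs from slight at 0.001 to severe at 0.05. All of this rests on assumed ICCs, equal control sites, a two-sided 5% test and known between-hospital variance.

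For the feasibility study, the consequence is a modest to moderate excess of false positives if the comparison is tested ignoring hospital, not a broken power claim. The inseparability of programme and hospital rests on none of these assumptions and applies to aim 1 as it stands. The point should be fixed, but it does not block a feasibility study whose other aims concern recruitment, retention, measures and stakeholder feedback.

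**What to change.** In Sample Size and Power Analysis:

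- State that 180 complete (240 recruited) per arm assumes no variation between hospitals.
- Give the assumed significance level, and tabulate power for one versus four hospitals over an ICC range that includes 0.001 to 0.05.
- State that 240 per arm is not to be carried forward as the larger study's requirement without an ICC and a number of hospitals per arm, with more than one intervention hospital.

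For aim 1, and where the design is justified, describe the result as a difference between the hospital with the programme and the regional hospitals without it, not as an effect attributable to the programme.

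The cost is a less favourable stated figure and a narrower claim; no extra children, sites or data are needed. Adding the second funded hospital to the feasibility study is optional. It would need another site's agreement and the associated recruitment and interviews, and it is not part of the required change.

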### Data Analysis

The primary and secondary outcomes form the dependent variables in this research. The independent variables include being in receipt of the intervention or not being in receipt of the intervention (i.e., membership of either the intervention or the control group).

Quantitative data will be analyzed descriptively. Continuous or scale data will be analyzed using analysis of variance (ANOVA), and we will report group means and standard deviations. We will control for confounders as previously described. We will use the data and variables of the number and type of education support activities as a measure of dose and perform sensitivity analysis. Qualitative data obtained from stakeholder interviews will be analyzed thematically.

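### A 25% loss, called low and assumed equal in two non-randomised arms, feeds an ANOVA that ordinarily drops children with a missing visit; a mixed model using every available score is safer

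*Protocol article*

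**What the plan says.** Under Sample Size and Power Analysis, the study is sized to "have an 80% chance of detecting a 0.3 standard deviation effect of the intervention", and the requirement is put this way: "we would need complete data from 180 participants in each arm of the study". On loss, the text reads "Attrition and loss to follow-up is considered to be low, in the order of 25" per cent, and from this it concludes that "we would need to recruit 240 participants to each arm of the study". No source is given for the rate, and no separate rate by arm. The feasibility study itself recruits 40 per arm.

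Under 3-month and 6-month data, both outcomes are measured again at those two times after baseline. Under Data Analysis, the method is: "Continuous or scale data will be analyzed using analysis of variance (ANOVA), and we will report group means and standard deviations". Confounders are to be controlled for. Nothing is said about children with a missing visit.

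Under Study Design and Setting, the arms are one metropolitan children's hospital with the programme and four regional hospitals without it, not randomised. The Blinding section says that blinding is not achievable. Under The Present Study, trialling recruitment and retention is one of the four aims.

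**The concern.** Raising recruitment from 180 to 240 restores precision after loss. It does nothing about who is lost. If the same share leaves each arm, and leavers differ from stayers in the same way in each, the completer difference is unaffected. If the share differs by arm and leaving is related to the outcome, the two completer means shift by different amounts and their difference is wrong.

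Both conditions are plausible here. The arms are different hospitals with different services and families, and everyone knows which arm they are in. The primary outcome is self-reported school engagement, and the article's own definition of chronic illness includes deterioration and poor prognosis. Children who are disengaged or sicker may well be the ones who stop answering.

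The choice of ANOVA makes this worse than it need be. A repeated-measures ANOVA normally needs all visits. A separate ANOVA at 6 months ignores the 3-month score of a child who then leaves. Either way, collected data that say something about the missing value go unused.

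Two things are at stake: the effect estimate from this study, and the retention rate that the larger study would take over.

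**Working it through.** **Inputs from the protocol.** Power 80%, effect 0.3 SD, 180 complete per arm, loss 25%, 240 recruited per arm, 40 per arm in the feasibility study.

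**Inputs assumed.** Two-sided alpha of 0.05 (not stated); loss by arm; the correlation r between the tendency to stay and the outcome.

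**1. The plan's own figures.** n per arm = 2 × (1.960 + 0.842)² / 0.3² = 174.4, so 175; the t-test version gives 176. The stated 180 is close and gives 81% power. Inflation: 180 / (1 − 0.25) = 240, exactly as stated. A loss of 25% from 40 leaves 30 per arm.

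**2. Does unequal loss hurt power?** With 240 recruited per arm and mean loss kept at 25%:

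| Loss, intervention v control | Completers | Power |
|---|---|---|
| 25% v 25% | 180 v 180 | 81.2% |
| 20% v 30% | 192 v 168 | about 81% |
| 15% v 35% | 204 v 156 | 80.5% |

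Power barely moves, so the issue is bias.

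**3. Bias in a completer comparison.** Suppose that the share p with the lowest tendency to stay is lost, and that this tendency correlates r with the outcome. The completer mean then lies above the full-arm mean by r × λ(p), where λ(p) = φ(z_p) / (1 − p). The error in the difference (intervention minus control) is r × [λ(p_I) − λ(p_C)].

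- λ(0.15) = 0.2332 / 0.85 = 0.274
- λ(0.20) = 0.2800 / 0.80 = 0.350
- λ(0.30) = 0.3477 / 0.70 = 0.497
- λ(0.35) = 0.3704 / 0.65 = 0.570

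| Loss, intervention v control | r | Shift in each arm (SD) | Error in difference (SD) |
|---|---|---|---|
| 20% v 30% | 0.2 | 0.070 v 0.099 | −0.029 |
| 20% v 30% | 0.5 | 0.175 v 0.248 | −0.073 |
| 15% v 35% | 0.2 | 0.055 v 0.114 | −0.059 |
| 15% v 35% | 0.5 | 0.137 v 0.285 | −0.148 |

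The last line is 0.148 / 0.3 = 49% of the target effect. The sign is negative because low scorers are assumed to leave and the control arm to lose more. If the intervention arm lost more of them, the sign would be positive.

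**4. A second, simpler model.** If leavers score g SD below stayers in both arms, the error is g × (loss in intervention − loss in control). With g = 0.5, this gives −0.05 SD at 20% v 30% and −0.10 SD at 15% v 35%. With g = 0.2, it gives −0.02 and −0.04 SD. The size is similar.

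**5. Does the proposed model help?** Take a true effect of 0.30 SD at both follow-ups, a correlation of 0.5 between the 3- and 6-month scores, and loss before 6 months of the lowest 15% (intervention) and lowest 35% (control) on the 3-month score. The completer difference at 6 months is 0.30 − 0.148 = 0.15 SD. A likelihood analysis predicts the missing 6-month scores from the 3-month scores of all children, using the completers' regression, and returns 0.30 SD. The full correction occurs because loss here depends only on a recorded score.

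**The case against.** The strongest reply is that much of this is inference. The phrase about complete data is a sample size requirement, and a reader might infer from it that only complete cases will be analysed. The article does not say so. Missing-data rules are commonly left to an analysis plan, and none is shown. That stands: the point is about the method that is named, ANOVA, and what it ordinarily does with a missing visit.

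A reader might also infer that only the intervention arm keeps in touch with families after discharge, which would make unequal loss nearly certain. Table 1 does not support this. Its wording about "needs continue to be identified and met throughout their healthcare journey: hospital, home and return to school" belongs to liaison with teachers. The family activities carry no post-discharge wording, and research follow-up at 3 and 6 months covers both arms. Unequal loss is plausible because the hospitals differ, but no cause for it is documented.

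It is also fair to say that the loss rates and correlations are assumed, that 0.15 SD is the extreme of the range, and that the planned confounder adjustment might remove part of the bias. Retention is an aim of this study, so the 25% is to be tested and not simply inherited. With about 30 completers per arm, the 95% half-width for a difference is 1.96 × √(2/30) = 0.51 SD, well above the bias computed here. These arguments limit the size and urgency of the point. They do not make ANOVA the better choice, because the bias does not shrink as the sample grows and the larger study would probably reuse the method.

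**Conclusion.** The point holds in a limited form. The 25% is unsupported, described as low, and applied equally to two arms for which equality has no basis in the text. The named analysis would ordinarily discard part of the repeated data, and a better one is available at little cost. Under the assumed ranges (20% v 30% to 15% v 35%, r from 0.2 to 0.5), the error in the between-arm difference is about 0.03 to 0.15 SD, or 10% to 50% of the 0.3 SD target. It understates the effect if low scorers leave the control arm more, and is zero if loss and its relation to the outcome are the same in both arms.

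The sample size itself is not in error: 180 and 240 both reproduce. The retention aim already covers much of the concern about carrying the rate forward. What it lacks is the commitment to look at retention by arm.

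**What to change.** Under Data Analysis, replace the ANOVA with a repeated-measures mixed model. Its terms are arm, time, arm by time, the baseline score and the confounders already planned. Include every child with a baseline score and at least one follow-up score. Group means and standard deviations can still be reported alongside.

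Under Sample Size and Power Analysis, describe 25% as a planning assumption and remove the description of it as low. State that retention at 3 and 6 months will be reported by arm, with baseline engagement, quality of life, diagnosis and socio-economic position compared between children retained and lost, before any rate is carried to the larger study.

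The cost is one model in place of another, a few sentences, and one table from data already to be collected. There are two limits. The model assumes that loss depends only on observed data, and a child lost before 3 months contributes no follow-up score, so the table of retained and lost children is needed to judge that part. With 40 per arm, retention by arm will also be imprecise: 10 lost of 40 has an exact 95% interval of about 13% to 41%.
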